### Randomization

2.6

Randomization occurs after the eligibility assessment and completion of the V1 and associated questionnaires mentioned below. Group allocation is concealed using online computerized randomization by FANI (*Application Fonctionnelle de Nutrition sur Internet*), a Web platform developed and hosted by the Institut sur la nutrition et les aliments fonctionnels, Université Laval. Eligible subjects will be randomized to the intervention or control group at a ratio of 1:1. The randomization order is generated independently using online computerized group allocation with a permuted block of variable block sizes (4–10). The participant’s treatment allocation is then automatically and electronically delivered to the local site investigator and research staff. Randomization is performed over the phone with the candidate after confirmation of her willingness to participate. Group allocation is then provided immediately to the participant.

#### Intervention arm

2.6.1

The development of the suggested intervention was intricately woven with principles drawn from a conceptual model based on health behavior change theory during pregnancy and illustrates some key elements with motivation and self-efficacy as central health behavior change constructs (46) in facilitating the transformation of pregnant individuals’ dietary habits. Furthermore, the intervention was thoughtfully aligned with the latest guidance provided by the CFG. It encompasses a three-tiered approach designed to empower expectant mothers with the knowledge, skills, and motivation necessary for optimal diet during pregnancy.

The main component of the suggested intervention is four individual 1-h in-person (or virtual, according to participants’ preference) counseling sessions conducted by an RD at key junctures in the pregnancy journey (12, 18, 24, and 30 weeks). The RD uses motivational interviewing which has been has been shown to have had promising results when used in nutritional interventions (47–50). Nutritional counseling during pregnancy is not only the most effective intervention for improving pregnant women’s knowledge and understanding but could also prevent multiple perinatal complications (51–53). Within the individualized counseling sessions, participants will be encouraged to elaborate Specific, Measurable, Attainable, Relevant, Timely (S.M.A.R.T.) goals regarding their eating habits per the CFG guidelines. Hence, every participant’s goals will be tailored to their own verbalized priorities and motivations to improve compliance. During these counseling sessions, the RD will also help participants to identify potential barriers and solutions to achieve their goals. Between the individual counseling sessions, four phone call follow-ups with the RD will be provided to review the goals and solutions chosen by participants (15, 21, 27, and 33 gestational weeks).

The intervention also includes access to 10 informative brief video clips about healthy eating during pregnancy, which are hosted on a private Web platform. The video clips were developed by a team of RDs from our research team, in line with the data demonstrating that (1) education is a necessary component for behavior change (54), and (2) the lack of available resources appears to be a key barrier to healthy eating (55, 56). Their conception also involved experts in prenatal nutrition, communication, and three patient partners. The content was based on current evidence, as well as, on national and provincial recommendations including the CFG and both Health Canada and Quebec National Institute of Public Health’s guidelines for pregnancy. These brief (4–14 min) and informative nutritional video clips cover concerns about healthy eating throughout pregnancy and aim to increase nutrition knowledge to improve motivation (57) and facilitate the achievement of their set goals. The video clips have the following title and the development process as well as their content is available in Supplementary Tables S1, S2.

The importance of healthy eating during pregnancyShould we eat differently during pregnancy?General recommendations for healthy eatingFood precautions to take during pregnancyHealthy eating habitsWhy and how to favor minimally processed foods?The influence of the food environmentDiscomforts during pregnancy: what is the role of food?Nutrients for a healthy dietA better understanding of nutrition labeling

Lastly, participants randomized to the intervention group are invited to join an online private virtual community on Facebook to discuss and share experiences, thus maintaining motivation and providing social support, as requested by pregnant individuals (58). The Facebook group is animated and moderated by an RD. Each week, the RD shares a new publication that addresses one of the four dimensions of social support (emotional, instrumental, informative, and evaluative) (59) to guide the discussion between participants. This virtual support community was established to provide continuous motivation, peer support, and the exchange of experiences to bolster participants’ commitment to their nutritional goals.

This multi-dimensional approach aims to empower pregnant individuals to make positive and sustainable dietary choices throughout their pregnancy. Moreover, this intervention has been strategically designed to encompass a multitude of behavior change techniques, including goal setting, education, problem-solving, coping planning, and social support (60). By incorporating these techniques, the intervention aims to create a comprehensive framework that not only educates and informs but also enables and supports pregnant individuals in their journey toward healthy eating during pregnancy. These techniques are thoughtfully intertwined within the counseling sessions, the video clips, and the virtual support community, fostering motivation, self-efficacy, and the development of practical skills necessary for achieving and maintaining optimal dietary practices. The synergistic effect of these techniques provides a robust foundation for behavior change, ultimately enabling participants to make informed choices and establish healthy eating habits during pregnancy.

The chosen time frame for intervention commencement (12 weeks), was determined in accordance with the Canadian perinatal care practices. In most cases, contact with medical professionals for pregnant individuals does not occur until around 10–12 weeks, coinciding with the confirmation of pregnancy through ultrasound assessments, such as nuchal translucency and dating ultrasound. Additionally, it is well-acknowledged in medical literature that a significant proportion of miscarriages occurs within the first 12 weeks of pregnancy. Considering these factors, initiating the intervention at 12 weeks allows for a more stable participation, reducing the risk of early dropouts due to miscarriage.

The chosen hybrid mode of delivery, combining in-person, virtual, and phone counseling, is based on previous studies suggesting that in-person counseling with multiple visits might not be feasible and can decrease treatment efficacy (61). The use of Web-based resources to provide nutrition information is based on the reported preferences of French-Canadian pregnant individuals (62). Data also suggest that evidence-based online educational interventions are credible, low cost, and easily accessible, while also complementing the advice provided by healthcare providers (56).

Our choice to prioritize nutrition intervention, rather than covering areas such as physical activity or other lifestyle habits, is primarily based on the simplification of the intervention that takes into account the reality that pregnant individuals are often faced with a multitude of responsibilities and concerns, which can lead them to feel overwhelmed, especially as their time to meet with several health professionals is limited (63). This simpler approach aims to enhance adherence to the program and facilitate the achievement of individual goals and have the potential to be implemented with perinatal care. This choice is also based on the fact that diet-based interventions have been associated with a reduced risk of GDM while mixed-approach interventions seem to be less effective (64). Moreover, current literature clearly demonstrates that pregnant individuals are motivated to eat well during pregnancy and require help to do so (65, 66). Finally, by choosing to target nutrition, we also avoid having to interrupt the intervention due to physical activity contraindications (67, 68). However, we do not deny the importance of staying active during pregnancy, which is suggested by recent Canadian recommendations (67). Physical activity will be measured every trimester to control for this confounding factor. Participants having questions about physical activity will be referred to their general practitioner or a kinesiologist.

#### Control arm

2.6.2

Participants randomized to the control group receive usual prenatal care from their general practitioner without access to the nutritional intervention. The usual prenatal care provided to all pregnant individuals in the Province of Quebec is provided by general practitioners, midwives, and obstetricians in private practice, family medicine groups, or in hospitals or birthing centers. Pregnant individuals in Quebec are encouraged to seek prenatal care early in their pregnancy and to meet with a healthcare provider or midwife as soon as the pregnancy is confirmed. Individuals have the option to choose between receiving care from a family doctor, obstetrician, or midwife, depending on their preferences and specific health needs. Midwives provide care as part of a team approach and are available for low-risk pregnancies. Throughout pregnancy, individuals attend a series of prenatal visits with their chosen healthcare provider. The frequency of these visits may vary but typically consists of monthly visits in early- and mid-pregnancy and bimonthly visits in late pregnancy. These visits generally include health assessments, monitoring of fetal development, discussions about pregnancy-related topics, and various routine tests and screening, such as ultrasound and blood tests. Usual prenatal care also involves education and counseling on topics such as childbirth preparation, breastfeeding, and postpartum care. Expectant mothers can also receive guidance through web-based or printed documents from national, provincial, or local resources, which can provide information on the reasons and ways to achieve and maintain a balanced diet and proper nutrition during pregnancy. They may be referred to RDs if considered necessary by their healthcare provider. In general, individuals carrying more than one fetus and those with complex medical histories (including a history of bariatric surgery or eating disorders), pre-existing health problems and GDM can be referred to an RD during pregnancy for appropriate dietary management. As a result, only a small proportion of pregnant individuals in Quebec have access to nutritional management as part of their usual prenatal care.

#### Both groups

2.6.3

Participants with a positive diabetes diagnosis in the first trimester are excluded. However, if a GDM is diagnosed during the second or third research visits, participants remain in the project. In the second and third trimesters (V2 and V3), GDM will be diagnosed using the alternate one-step approach suggested by Diabetes Canada’s latest guidelines and the International Association of the Diabetes and Pregnancy Study Groups based on the Hyperglycemia and Adverse Pregnancy Outcome study (5). Therefore, GDM will be diagnosed if one plasma glucose value is abnormal (FPG ≥ 5.1 mmol/L, 1 h following the ingestion of 75 g of glucose ≥10.0 mmol/L, 2 h following the ingestion of 75 g of glucose ≥8.5 mmol/L) (2). The usual conduct for GDM management is to refer to the multidisciplinary team for pregnancies at risk in hospitals or clinics and nutritional therapy is usually initiated within a few weeks (2). Hence, participants diagnosed with GDM will be referred and followed by a multidisciplinary team including RDs, regardless of their group allocation. Since the diagnosis of GDM in the second trimester and the resulting treatment received by the participants may interfere with our results, the effect of this added care will be monitored through retrospective patient medical record data collection and considered in our statistical analyses. However, a late diagnosis at V3 and its subsequent management are not expected to interfere with the results collected at V3 and will therefore not be considered in analyzing our primary and secondary outcomes. Participants are also instructed to contact the research staff between visits or phone calls if they are diagnosed with GDM outside of research visits or if any relevant situations occur during their participation, making them no longer eligible for the study or unable to complete their participation.

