### Gestational diabetes mellitus prevalence, complications, and treatment

1.1

Gestational diabetes mellitus (GDM) is the most frequent health condition among pregnant individuals. Its prevalence is increasing worldwide, as it can reach up to 20% of pregnant individuals in some parts of the world, depending on their risk factors and the methods used to screen and diagnose GDM (1, 2). This condition is associated with adverse consequences such as fetal macrosomia, obesity, and glucose intolerance in the offspring, as well as higher risks of type 2 diabetes, metabolic syndrome, and cardiovascular diseases for the mother (3, 4). In addition, independently of a frank GDM diagnosis, even mildly elevated glucose levels can lead to negative effects on the health of the mother and child (5). Indeed, there is a strong and continuous association between third-trimester maternal glucose levels and increased birth weight as well as other pregnancy complications, even below the threshold of GDM diagnosis (5).

In Canada, routine screening for GDM is part of the usual pregnancy care and is recommended to all Canadian pregnant individuals between 24 and 28 weeks of gestation (6). The first-line treatment of GDM involves medical nutritional therapy and management provided by registered dietitians (RDs) in primary care, along with glucose self-monitoring (6). In practice, pregnant individuals with GDM are encouraged to follow the general recommendations of the 2019 Canada’s Food Guide (CFG), with particular attention to carbohydrate, fiber, and protein intake (6, 7). This type of intervention, alongside exercise, can be sufficient to improve the glycemic profile and to achieve glycemic goals in a high number of cases. However, for some individuals, pharmacological therapy is required to ensure the maintenance of adequate glycemic control (3, 6, 8). Moreover, nutritional therapy is generally initiated in the last trimester, thus limiting the potential benefits to a short period, and only those with a confirmed GDM diagnosis are referred to an RD. Therefore, most Canadian individuals at risk for GDM do not have access to nutritional therapy during their prenatal care. This situation is unfortunate because a high number of pregnant individuals, particularly those with a pre-pregnancy BMI ≥ 30 kg/m^2^, remain at an elevated risk for other pregnancy complications, including cesarean section births and higher birth weights (9).

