### Participants eligibility

2.3

Individuals who meet the following inclusion criteria can participate in the study:

Aged ≥18 years;Being at ≤14 weeks of gestation with a singleton pregnancy at the first visit (Visit 1 [V1]); andPresenting a risk factor for GDM according to Diabetes Canada guidelines (2): being (a) 35 years of age or older or (b) from a high-risk group (African, Arab, Asian, Hispanic, Indigenous, or South Asian), or having (c) obesity (pre-pregnancy BMI ≥ 30 kg/m^2^), (d) prediabetes, (e) GDM in a previous pregnancy, (f) given birth to a baby that weighed more than 4 kg, (g) a parent, brother or sister with type 2 diabetes, (h) polycystic ovary syndrome, or (i) acanthosis nigricans.

Individuals presenting at least one of the following exclusion criteria will not be eligible to enroll in the study:

Having a diagnosis of overt diabetes mellitus or early GDM at V1.Diagnosed with an active disease requiring nutritional therapy influencing glucose metabolism or with uncontrolled eating disorders that would interfere with the initiation of intervention.Planning for or history of bariatric surgery, which would confound the impact of the nutritional intervention tested.Planning for or engaging in another nutritional intervention program, which would also confound the impact of the nutritional intervention tested.Using a medication affecting glucose metabolism (such as metformin or, corticosteroids), which may confound the primary outcomes of this study.Inability to understand and communicate in French.Unable to attend research visits at the participating center for the next 9 months.

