#### Glucose homeostasis outcomes

2.7.1

At each visit, glucose, insulin, and C-peptide will be measured on fresh blood samples drawn after a 12-h fast, as well as 15, 30, 60, and 90, 120 min after the ingestion of 75 g of glucose. Glucose will be measured enzymatically by the hexokinase method whereas insulin and C-peptide will be measured with an electrochemiluminescence immunoassay. The obtained data will be used to calculate the incremental area under the curve for glucose (iAUC glucose) using the trapezoid method from 0 to 120 min. The following indexes will also be calculated: HOMA-IS [Fasting insulin (μU/ml) × fasting glucose (mmol/L)/22.5] (39); Matsuda index {10,000/[fasting glucose × fasting insulin × (mean glucose × mean insulin)]^1/2^} (40); Insulinogenic index [(insulin at 30 min − fasting insulin)/(glucose at 30 min fasting glucose)] (41). The disposition index, which serves as an integrated measure that reflects beta-cell function, will be calculated using Matsuda index × insulinogenic index (41). GDM incidence will be recorded throughout the study based on OGTTs performed during the research visits or based on medical records if not diagnosed during research visits detailed (2).

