#### Statistical analyses

2.10.2

The primary analyses will follow the complete case intention-to-treat principle. Changes from first- to third-trimester measurements of the primary and secondary outcomes between the intervention and control groups will be assessed using a two-sample one-sided *t*-test for means. To determine whether the results obtained depend on an improvement in diet quality, a generalized linear model will be used. Sensitivity analyses will be performed on all outcomes to (1) determine if missingness of the outcome data is associated with prognostic characteristics at baseline and treatment group; (2) compare the results obtained with those following an intention-to-treat analysis where missing outcomes are handled using multiple imputation by chained equations, an analysis on a complete case per protocol, and a per-protocol analysis where missing outcomes are handled using multiple imputation by chained equations; and (3) to explore potential sources of heterogeneity in treatment effects. We thus plan to test the effect of various covariables including age, pre-pregnancy BMI, parity, gestational weight gain, GDM risk factors, fasting blood glucose in the first trimester, GDM diagnosis in the second trimester, adherence to the intervention (with a weighted model based on the level of participation in the intervention), and intervention delivery mode (in person of virtually). Those analyses will ensure a more comprehensive understanding of how different factors may influence the intervention’s outcomes in diverse subgroups of the study population. Programming codes will be tested with a dummy data set to ensure their validity. No preliminary or interim analyses are planned. An exploratory health-economic analysis could be conducted *post hoc*.

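### V3 insulin-based indices are computed from assayed insulin even in participants on injected insulin, and the one covariable named does not deal with this

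*Protocol article*

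**What the plan says.** - **Retention and care (2.6.3, Both groups).** "if a GDM is diagnosed during the second or third research visits, participants remain in the project". In both arms, "participants diagnosed with GDM will be referred and followed by a multidisciplinary team including RDs, regardless of their group allocation". For treatment that follows a second-trimester diagnosis, "the effect of this added care will be monitored through retrospective patient medical record data collection and considered in our statistical analyses". A diagnosis at V3 is set aside because its management comes after the V3 sample.
- **Drug treatment is foreseen (1.1).** "for some individuals, pharmacological therapy is required to ensure the maintenance of adequate glycemic control". No proportion is given.
- **Such drugs are recognised as a confounder at entry (2.3).** One exclusion criterion reads "Using a medication affecting glucose metabolism (such as metformin or, corticosteroids), which may confound the primary outcomes of this study".
- **Index definitions (2.7.1).** "At each visit, glucose, insulin, and C-peptide will be measured on fresh blood samples drawn after a 12-h fast", and again at five times after the glucose load. HOMA, Matsuda and the insulinogenic index are written as functions of glucose and insulin. The disposition index is Matsuda times insulinogenic index. C-peptide enters none of the formulas, and no exception is made for participants taking insulin.
- **Analysis (2.10.2).** Changes in primary and secondary outcomes are compared by a one-sided two-sample t-test on complete cases. Among the covariables for the sensitivity analyses is "GDM diagnosis in the second trimester". Multiple imputation by chained equations is planned as a sensitivity analysis.
- **Data available.** Table 1 records medication use at V1, V2 and V3. Section 2.7.5.9 takes pregnancy complications and their management from medical records.

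**The concern.** HOMA, Matsuda and disposition index are named secondary outcomes for the first-to-third-trimester change. They are meant to describe the participant's own insulin sensitivity and beta-cell function. In someone injecting insulin at V3, the assayed value may include injected insulin, or may reflect suppressed secretion. In either case the printed formula no longer measures what section 1.5 says it measures.

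The affected values need not balance between arms. If the intervention prevents GDM, more control participants would be on insulin at V3, and the artefact would then enter the between-arm comparison. Section 2.6.3 recognises that treatment can interfere, but the variable that section 2.10.2 carries forward is diagnosis, not treatment.

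**Working it through.** **1. Base number.** The stated total is 150. With a difference of 0.4 and SD 0.8, d = 0.4/0.8 = 0.5. A one-sided t-test at 0.05 with 80% power needs 51 per arm, or 102. The stated losses are 4% + 8% + 20% = 32%, and 102/(1 − 0.32) = 150. The plan's figure reproduces, so about 51 completers per arm are expected.

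**2. How many could be on a drug at V3.** Number = 102 × GDM rate × share on drugs. The article gives GDM rates of 8% (Quebec, section 2.1) and up to 20% (section 1.1). The 30% to 40% rates for an at-risk cohort and the 10% to 50% drug share are assumptions.

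| GDM rate | 10% on drugs | 50% on drugs |
|---|---|---|
| 8% | 0.8 | 4.1 |
| 20% | 2.0 | 10.2 |
| 30% | 3.1 | 15.3 |
| 40% | 4.1 | 20.4 |

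These counts cover any glucose-lowering drug. Only the insulin users among them have the problem described here.

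**3. Effect on one participant's indices.** From the printed formulas, at fixed glucose, HOMA is proportional to fasting insulin (I₀). Matsuda is proportional to 1/√(I₀ × mean insulin). The insulinogenic index is proportional to (I₃₀ − I₀).

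*Case A: the assay reads injected insulin as a constant addition.* The assumed insulin profile is 10, 50, 70, 75, 65, 55 µU/mL (mean 54.17).

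| Added µU/mL | HOMA | Matsuda | Insulinogenic | Disposition |
|---|---|---|---|---|
| 5 | +50% | −22% | 0 | −22% |
| 10 | +100% | −35% | 0 | −35% |
| 20 | +200% | −51% | 0 | −51% |

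For 10 µU/mL, the Matsuda ratio is √[(10 × 54.17)/(20 × 64.17)] = √0.422 = 0.65. The addition cancels in I₃₀ − I₀.

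*Case B: the assay does not read injected insulin and own secretion falls by 30% at every time point.* HOMA × 0.7 (−30%), Matsuda × 1/0.7 = 1.43 (+43%), insulinogenic × 0.7, disposition 1.43 × 0.7 = 1.0 (unchanged).

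**4. Effect on an arm's mean V3 HOMA.** Take m insulin-treated participants, otherwise average, among 51. In Case A with HOMA doubled, the mean rises by m/51: 2%, 6% and 10% for m = 1, 3 and 5. In Case B it falls by 0.3m/51: 0.6%, 1.8% and 2.9%.

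**5. Does the named covariable reach this?**
- Diet-treated and insulin-treated cases diagnosed in the second trimester carry the same code.
- Section 2.6.3 deals with second-trimester diagnosis and with diagnosis at V3 (34–36 weeks). It also asks participants to report a diagnosis made outside research visits. A diagnosis made after the second trimester but before V3 falls under neither rule and not under the covariable.
- A covariable adjusts a comparison of outcomes. It does not restore the meaning of an index whose insulin input is wrong for that participant.

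**The case against.** The strongest reply is that the protocol sees the problem. Section 2.6.3 names treatment as well as diagnosis, commits to collecting it from records and promises to consider it. The algorithm may stand in an analysis plan that is not shown, and its absence from an article would be no finding. Keeping GDM cases is what intention to treat requires. The same section also mentions situations that make a participant no longer eligible, so it is unclear whether someone starting a drug would remain.

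Much of this stands. Retention is correct, and the commitment is real. The article nevertheless fixes the index formulas, the main test and the covariable, and those three together do not deliver what section 2.6.3 promises.

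A second reply is that a remedy can do harm. If these values are simply set to missing, the complete-case main analysis drops participants selected after randomisation, possibly more from one arm. That also stands, and the fix has to avoid it.

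Several stronger readings are tempting and not supported:
- *The secondary outcomes as a whole are invalid.* 2-h glucose and iAUC use no insulin value. First-to-second-trimester changes in those diagnosed at V2 precede treatment.
- *Any glucose-lowering drug spoils the indices.* A non-insulin drug adds no injected insulin to the sample. Whether to count its effect is a choice of estimand.
- *The fasting glucose result is compromised.* Analysing it regardless of treatment is a legitimate treatment-policy choice. Drug-lowered values among controls would shrink the contrast, not inflate it.
- *The insulinogenic index is always distorted.* A constant insulin addition cancels out of it.

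**Conclusion.** The point holds in narrow form. Followed as written, sections 2.7.1 and 2.10.2 give V3 HOMA, Matsuda and disposition values that do not describe endogenous sensitivity or secretion in participants on injected insulin. The one covariable named neither finds those participants nor repairs their values.

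The distortion can be large for an individual. Its effect on the arm comparison is undetermined. It depends on how many are on insulin, how they split between arms, and whether the assay reads the injected product, and the documents give none of these. Case A makes treated participants look worse, which would favour the intervention if more controls are treated. Case B makes them look better on HOMA and Matsuda and leaves the disposition index unchanged. The percentages rest on an assumed profile with glucose held fixed and should be read as illustration. Neither the primary outcome nor the sample size is called into question.

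**What to change.** 1. In 2.7.1 and 2.10.2, state that V3 insulin-based indices from samples taken while on exogenous insulin are not treated as valid observations. Handle them with the chained-equations model already planned, using V1 and V2 values, rather than letting them fall out as incomplete cases. State the assumption: given their earlier values, these participants' indices without injected insulin would have resembled those of comparable participants not on insulin. Report a supporting measure from the C-peptide already collected.
2. Keep all participants in the main analysis of fasting glucose, 2-h glucose and iAUC. Define the supplementary analysis by glucose-lowering drug treatment before V3, taken from the V1–V3 medication questionnaire and the medical records, instead of by second-trimester GDM diagnosis alone. Treatment before V3 is a workable definition because the article does not say that drug start dates are recorded.

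Cost: wording in two sections, one extra analysis and no new measurements. The downside is that a few index values are imputed under an assumption the data cannot fully test. The rule should be fixed before outcome data are analysed, since the trial is open-label.
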